The overall aim of the proposed research is to evaluate two different strategies for delivering HIV care and treatment services during the postpartum period to eligible HIV-infected women who initiate antiretroviral treatment (ART) during pregnancy and their HIV-exposed infants. The study’s primary objective is to compare an MCH-focused ART service to general adult ART services as strategies for providing ART during the postpartum period. The primary outcomes are (i) maternal HIV viral suppression, and (ii) maternal retention in ART services, at 12 months postpartum. Additional objectives focus on understanding the PMTCT ‘cascade’ (including the drop-out of ART-eligible women before delivery); investigating breastfeeding practices in the context of maternal ART use; MTCT rates at different times postpartum; and the acceptability and cost-effectiveness of the postpartum ART strategies under evaluation.

The study is to be conducted at the Gugulethu Midwife Obstetric Unit (MOU) in Cape Town. The study design has three interrelated phases.

- **Phase 1** is a cross-sectional evaluation of consecutive HIV-infected pregnant women seeking antenatal care at the study clinic (up to n=1600)
- **Phase 2** of the study is an observational cohort of all women from Phase 1 who are eligible for initiation of ART (up to n=600), followed in three study measurement visits, from their second antenatal clinic visit until their first postpartum clinic visit. ART initiation and antenatal follow-up takes place at the Gugulethu MOU according to standard provincial protocols.
- **Phase 3** of the study is a randomised trial of strategies for delivering ART to women during the postpartum period (the primary objective; n= up to 480). Women enrolled in Phase 2 who are breastfeeding their infants will be approached to participate in the trial at the end of the first routine postpartum clinic visit. Phase 3 will randomise women to one of two approaches to providing ART during the postpartum period to HIV-infected mothers who are breastfeeding:
  - Arm A: referral of women to their nearest general adult ART services at approximately 4-8 weeks postpartum (the current standard of care in this setting)
  - Arm B: continued receipt of ART in the antenatal clinic, as part of a MCH-focused ART service at the Gugulethu MOU that only refers women to general adult ART services after the end of breastfeeding and once infants' final HIV status is determined

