### **Secondary objectives**

- 2.1 To characterize the health status of the population of HIV+ pregnant women seeking antenatal care at the Gugulethu Midwife Obstetric Unit (MOU) including maternal and infant outcomes
- 2.2 To describe uptake and timing of services received throughout the PMTCT cascade, including antenatal ART initiation and follow-up, at the Gugulethu MOU
- 2.3 To examine whether there is variation in the impact of the two postpartum HIV care strategies on the primary outcome between subgroups of women according to their demographic, clinical and psychosocial characteristics, measured antenatally and postnatally.
- 2.4 To describe changes in women's clinical and/or psychosocial characteristics between the antenatal and postnatal periods, and investigate how these are independently associated with the primary outcome
- 2.5 To compare MCH-focused ART services to general adult ART services on:
  - a. Women's missed visits and loss to follow-up on ART up to 18 months postpartum
  - b. Breastfeeding practices, including duration of exclusive feeding and weaning patterns
  - c. Maternal viral suppression throughout the breastfeeding period as well as before and after cessation of breastfeeding
  - d. Infant health outcomes including growth parameters and incidence of respiratory and/or diarrhoeal illness
  - e. Rates of HIV transmission from mother-to-child at 6 weeks and 12 months postpartum
  - f. Acceptability of different strategies for delivering HIV care and treatment during the postpartum period
  - g. Cost-effectiveness in delivering HIV care and treatment during the postpartum period
  - h. Developmental scores of 1 year old infants

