#### Data analysis

Data will be exported to Stata Version 12.0 (Stata Corporation, College Station, Texas) or R (Gnu Project) for analysis. All analyses will be carried out under supervision by the study statistician. All outcomes will be blinded to investigators until the data are cleaned and data analyses completed.

As described above, the primary analysis population (up to n=390) is all women enrolled into Phase 3 of the study who initiated ART during pregnancy after 1 July 2013 when the new provincial PMTCT guidelines were implemented. The subset of women in Phase 3 who initiated ART before this time (n=90, approximately) will contribute to a secondary analysis population comprised all women initiating ART in pregnancy and enrolled into Phase 3 during the study period (up to n=480).

For the primary objective, we hypothesize that women in the MCH-focused ART group will be more likely to be retained in care (defined as attending ART clinical appointments and/or medication refill visits in the window between 9 and 12 months postpartum) and maintain viral suppression (defined as <50 copies/mL, with secondary analyses at other thresholds) at 12 months postpartum, compared to women randomized to the general adult ART group. Comparisons of study groups at enrolment will be stratified by duration of ART during antenatal period (i.e., prior to randomization), and will examine demographic and HIV-related variables. Comparison of outcomes will be based on Fisher's exact test, comparing the proportion of women in each arm reaching the primary endpoint and its components; all statistical tests for the primary analysis will be two-sided at  $\alpha=0.05$ . Analyses will be by intention-to-treat, with secondary analyses stratified by duration of postnatal follow-up in the MCH-ART arm. The duration of viral suppression during the postpartum period will be defined as cumulative study time with a documented VL<50 copies/mL (with sub-analyses for <400 and <1000 copies/mL). Kaplan-Meier methods stratified by study group will be used to describe time to detectable viraemia and time to defaulting care, with proportional hazards models used to examine the independent influence of participant characteristics. Note that primary analyses will draw only on women enrolled into Phase 1 and initiating ART after 1 July 2013; women initiating ART before this time will be included as a secondary analysis population for selected analyses.

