To address secondary objectives 2.1 and 2.2, data analysis of routinely collected measures of participants' use of PMTCT and ART services collected as part of Phases 1 and 2 will focus on the description of proportions of women receiving specific PMTCT services, and the delays calculated between various steps in the PMTCT cascade, including CD4 enumeration, return of CD4 results to patients and referral for ART, and initiation of ART. These analyses will employ proportions with exact 95% confidence intervals, and median delays (in days) with interquartile ranges. We will compare the proportions of women completing steps in the ART cascade, and the delays to specific steps, by basic demographic, psychosocial and clinical characteristics, collected during Phases 1 and 2. Comparisons will employ exact tests or rank-sum tests, as appropriate; statistical tests will be 2-sided at  $\alpha=0.05$ .

To address secondary objective 2.3, we will compare the two strategies for delivering ART during the postpartum period within subgroups of patients based on demographic, clinical and psychosocial characteristics measured antenatally (during Phase 2) and/or postnatally (during Phase 3). *A priori* subgroups will include:

- *Demographic characteristics* (age; gravidity/parity; education)
- *Clinical history & characteristics* (timing of HIV diagnosis; prior PMTCT or ART exposure)

- *Psychosocial characteristics* (measures of mental health and substance abuse; HIV- and ART-related knowledge and beliefs; adherence self-efficacy; perceived social support; disclosure of HIV status and ART use)
- *Antenatal ART use* (including duration of ART before delivery; adherence to ART during antenatal period)

Note that we will not adjust  $\alpha$  for multiplicity but will name these as *a priori* subgroup analyses that are secondary to the primary comparison of interest (in the overall intention-to-treat population).

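### Cascade delays are compared by median and rank-sum test with no rule for women who never complete a step, so the delay comparison (though not the completion comparison) can be attenuated or even reversed when completion differs between subgroups

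*Protocol*

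**What the plan says.** Objective 2.2 (section 2, Secondary objectives) is "To describe uptake and timing of services received throughout the PMTCT cascade, including antenatal ART initiation and follow-up". The Study synopsis lists the cascade among the additional objectives, "including the drop-out of ART-eligible women before delivery". Non-completion of steps is therefore expected and is itself of interest.

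Section 10, Data analysis, fixes the method. The steps timed are described as "including CD4 enumeration, return of CD4 results to patients and referral for ART, and initiation of ART". For the summaries it says "These analyses will employ proportions with exact 95% confidence intervals, and median delays (in days) with interquartile ranges". For subgroups of women it says "We will compare the proportions of women completing steps in the ART cascade, and the delays to specific steps", and "Comparisons will employ exact tests or rank-sum tests, as appropriate".

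Two outputs are thus planned for each step: the proportion completing it and the delay to it. The text does not say how a woman who never completes a step enters the second output. It names no censoring, competing event or rank for her. The same section does use time-to-event methods after delivery: "Kaplan-Meier methods stratified by study group will be used to describe time to detectable viraemia and time to defaulting care".

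**The concern.** A woman who never starts ART, or who delivers or is lost first, has no delay in days. A plain median, interquartile range or rank-sum test can use only observed delays, so on the ordinary reading these women drop out of the timing analysis. They are not a random subset. When observation of an antenatal step ends at delivery or loss, the longest delays are the ones most often cut off, and more are cut off in a slower subgroup or in one with more drop-out.

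At stake is the timing half of objective 2.2. A subgroup that takes longer and completes less often could be reported as about as quick as the others, or quicker. The completion half is not distorted.

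**Working it through.** The protocol states no figure for this analysis, so there is nothing to reproduce. It gives no delay distribution, drop-out rate or time from booking to delivery. All rates below are assumptions, used to show direction and range.

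**1. Cut-off at delivery only.** Assume exponential delays and observation ending 16 weeks after the preceding step. If a proportion p completes, the rate is r = −ln(1−p)/16 per week. The median over all women is ln2/r, and the median among completers is −ln(1−p/2)/r.

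| p | r per week | median, all women (weeks) | median, completers (weeks) |
|---|---|---|---|
| 0.90 | 2.303/16 = 0.1439 | 4.8 | 0.598/0.1439 = 4.2 |
| 0.80 | 1.609/16 = 0.1006 | 6.9 | 0.511/0.1006 = 5.1 |
| 0.70 | 1.204/16 = 0.0752 | 9.2 | 0.431/0.0752 = 5.7 |

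For 90% against 70%, the difference in medians falls from 4.4 to 1.6 weeks. For 90% against 80%, it falls from 2.1 to 0.9 weeks.

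**2. The same cut-off with short delays.** With a cut-off at 112 days and a true median of m days, p = 1 − 2^(−112/m).
- m = 7: p is almost 1 and the completers' median is 7.0 days.
- m = 14: p = 1 − 2^(−8) = 0.996 and the completers' median is 13.9 days.
- m = 21: p = 0.975 and the completers' median is 20.3 days.

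The bias from the cut-off is negligible here.

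**3. Drop-out before delivery.** With completion hazard L and independent drop-out hazard M, the completers' median is ln2/(L+M). Take true medians of 28 and 56 days, no drop-out in the first group, and a drop-out hazard equal to the completion hazard in the second, so that half complete. The completers' medians are 28 days in the first group and ln2/(ln2/56 + ln2/56) = 28 days in the second. A twofold difference disappears.

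**4. Both together, by simulation.** There were 2000 runs with 300 women per group, exponential delays, delivery 56 to 196 days after the start, and drop-out stated per 140 days. The last three columns give the share of runs with p < 0.05.

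| True medians (days) | Drop-out | Completing | Completers' medians (days) | Rank-sum, completers | Log-rank, all women | Exact test on completion |
|---|---|---|---|---|---|---|
| 28 v 42 | 20% v 20% | 88% v 79% | 24.2 v 31.5 | 75% | 99% | 83% |
| 28 v 42 | 20% v 60% | 88% v 66% | 24.1 v 26.7 | 15% | 99% | 100% |
| 28 v 42 | 20% v 80% | 88% v 56% | 24.1 v 23.0 | 6.5% | 98% | 100% |
| 28 v 42 | 20% v 95% | 88% v 43% | 24.1 v 17.9 | 69%, order reversed | 96% | 100% |
| 28 v 28 | 20% v 80% | 88% v 67% | 24.1 v 18.5 | 69%, false difference | 5% | 100% |
| 7 v 10 | 20% v 60% | 98% v 91% | 6.9 v 9.1 | 82% | 99% | 98% |

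The log-rank test censors drop-out and delivery. It recovers the underlying delay here because the simulated drop-out is independent of the delay.

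**The case against.** **The protocol does not say completers only.** A reader might infer that it does. It does not: this is the ordinary reading of the named methods, not the plan's text. A rank-sum test can place non-completers last, and a median over all women exists when more than half complete. An analysis plan not shown could set such a rule. This limits the point but does not remove it, because the protocol chose the summary and the test, and it names censoring-based methods only for other outcomes.

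**Drop-out is already reported.** A reader might infer that the plan hides the subgroups that drop out most, or that real differences go unnoticed. The documents do not support that. Completion is compared by exact test across the same characteristics. With 90% against 80% completing and 250 women per group, repeated simulations of the 16-week model gave:
- rank-sum on completers: 41% to 45% power
- exact test on completion: 85% to 88%
- at least one of the two, unadjusted: 92%
- rank-sum with non-completers ranked last: 92%
- log-rank on all women: 95% to 96%

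At 90% against 70%, rank-sum on completers alone had 81%. This objection stands for the cascade as a whole. It does not rescue the delay estimates, since a completion proportion is not a delay.

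**Delays are probably short for most women.** Section 6 has CD4 blood drawn at the first antenatal visit and women not yet on ART starting at once. Section 3 has CD4 results available by the second visit. This stands for women enrolled under the policy in force from 1 July 2013, although the interval to the second visit is not given. It is less secure for the women enrolled earlier under CD4-based eligibility, about 300 in Phase 1 and 100 in Phase 2 (section 10, Sample size considerations). Against the maxima of 1600 and 600, that is 300/1600 = 19% and 100/600 = 17%.

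**Delivery need not end observation.** Sections 5 and 11 allow records to be abstracted after delivery, so the 16-week cut is an assumption. Even so, an antenatal step not taken before delivery has not been completed antenatally, and the plan gives no rule for it.

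**Conclusion.** The point holds in a limited form. As written, the delay comparison has no place for women who never complete a step. On the ordinary reading it is attenuated when completion differs between subgroups, and under strongly unequal drop-out it can be reversed. The completion comparison is sound.

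The size cannot be fixed from the protocol. It is small where steps are same-visit or next-visit. It could be material where delays run to weeks, possibly among women enrolled before 1 July 2013. The illustrative figures rest on exponential delays, independent drop-out and assumed rates, and should not be read as a forecast for this cohort.

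The priority is minor. Objective 2.2 is secondary and descriptive, the affected contrasts are between subgroups of women and not between randomised arms, and the primary comparison is unaffected.

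**What to change.** In section 10, Data analysis, under objectives 2.1 and 2.2:

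- Analyse each delay as time to event from the preceding step, in all women who reached that step. Censor loss to follow-up, and treat delivery before completion as a competing event for antenatal steps.
- Report cumulative incidence at fixed times, for example 7, 14 and 28 days.
- Compare subgroups by log-rank or Gray's test, and say which. The log-rank test compares completion rates among women still at risk, and Gray's test compares the cumulative proportion completing. A rank-sum test with non-completers ranked last is acceptable if it is described as a joint comparison of completion and speed. In the simulated case with equal true delays and 20% against 80% drop-out, it rejected in 85% of runs.
- If a completers-only median is kept, label it as such and print it beside the completion proportion and its denominator.

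The cost is analysis wording only. The planned medians already need the step dates, and section 8 already lists ART initiation, delivery and follow-up visit dates for abstraction. No visit, measurement or sample size changes.

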### *Randomization*

Randomization will take place at the end of the study measurement visit within the first week postpartum. Randomization will follow a dynamic permuted block design. Randomization numbers will be generated prior to the start of the study, and placed in sequentially numbered opaque envelopes. Randomization envelopes will be stored in a locked cabinet in the study office at UCT that will be accessed by the study coordinator when a woman is fully consented and has completed the immediate postpartum study visit, with independent documentation of the participant ID number, randomization date, and randomization assignment. The study coordinator will provide the MOU-ART service with a regularly updated list of women to be retained within the MOU-ART service until they have ended breastfeeding. The study coordinator involved in randomization will not be involved in interviewing participants.

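### Objective 2.3 lets effect-modification subgroups be defined by psychosocial measures taken after randomisation, and a separate secondary analysis stratifies on follow-up time that exists only in the MCH arm

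*Protocol*

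**What the plan says.** Objective 2.3 (Protocol, Section 2, Secondary objectives) is "To examine whether there is variation in the impact of the two postpartum HIV care strategies on the primary outcome between subgroups of women", the subgroups being formed on characteristics "measured antenatally and postnatally". Section 10, Data analysis, repeats this: the plan is to "compare the two strategies for delivering ART during the postpartum period within subgroups of patients", with characteristics "measured antenatally (during Phase 2) and/or postnatally (during Phase 3". The psychosocial group on the list is: "measures of mental health and substance abuse; HIV- and ART-related knowledge and beliefs; adherence self-efficacy; perceived social support; disclosure of HIV status and ART use". The same text says that alpha is not adjusted and that these analyses are a priori and secondary to the overall comparison.

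On timing, Section 8, Randomization, says: "Randomization will take place at the end of the study measurement visit within the first week postpartum". That visit is visit 4, the last of Phase 2. The first Phase 3 measurement is at 6 weeks postpartum.

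Separately, for the primary objective, Section 10 adds to the intention-to-treat analysis "secondary analyses stratified by duration of postnatal follow-up in the MCH-ART arm". It does not define duration or state a comparator.

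**The concern.** A subgroup comparison keeps the protection of randomisation only if allocation could not have changed who falls into the subgroup. Under Section 7, women in Arm B get continuing counselling on adherence, transmission risk and feeding at each MOU visit, so self-efficacy, beliefs, knowledge or mood measured later may plausibly differ by arm. Women with high self-efficacy in Arm B would then be a different mix from women with high self-efficacy in Arm A.

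The duration analysis has a related problem. Time in the MCH service arises after randomisation and has no counterpart in Arm A. Retention is one component of the endpoint, so a woman who leaves care early may have both a short duration and a failed outcome. A finding that longer stay goes with better outcome would bear directly on how long services keep women, and it could appear with no benefit of the strategy.

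**Working it through.** **Which subgroups are exposed.** From the list in Section 10 and the schedule of measurements in Section 8:

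- Age, gravidity/parity, education, timing of HIV diagnosis, prior exposure, antenatal ART duration and antenatal adherence are fixed before allocation. They are not affected.
- Knowledge inventories and medication beliefs: visit 2 (before allocation); 6 weeks and 9 months (after).
- K-10 and EPDS: visit 2; then 6 weeks, 12 and 18 months.
- Self-efficacy: visits 2 and 3; then 6, 12 and 18 months.
- Alcohol/substance use and social support: visits 2 and 3; then 6 and 12 months.
- HIV disclosure: asked in the Phase 2 questionnaires and again in Phase 3.

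So each psychosocial factor has a reading before randomisation, and some later readings coincide with or follow the 12-month outcome.

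**Size of bias from a postnatal measure (illustrative).** Assumptions: 195 women per arm (390/2, Section 10); a latent adherence tendency U, standard normal; postnatal measure high if U + shift × arm + standard normal noise > 0; logit of failure = −1.45 − 1.2U in both arms, giving about 24% failure and no arm effect; Fisher's exact test; 3,000 simulated trials. Bias is the failure risk in Arm B minus that in Arm A.

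| Shift in measure due to arm (SD of U) | Low stratum | High stratum | At least one significant subgroup |
|---|---|---|---|
| 0 | 0.0 points | 0.0 points | 8% |
| 0.5 | +3.7 | +2.2 | 11% |
| 1.0 | +8.2 | +4.5 | 26% |

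The overall comparison stayed unbiased throughout. In this model Arm B looks worse in both strata, because the shift moves lower-adherence women into its high stratum.

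**Duration of follow-up, null model.** Assumptions: 25% default by 12 months in both arms (the control failure rate in Section 10, treated entirely as default), constant hazard, weaning exponential and independent of default.

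Probability of no default by t months: S(t) = 0.75^(t/12), so S(3) = 0.9306.

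*Duration = earlier of default and weaning:*
- 6 months or more: failure = 1 − S(12)/S(6) = 1 − 0.75^0.5 = 13%.
- 9 months or more: 1 − 0.75^0.25 = 7%.
- Under 3 months: failure = [(1 − S(3)) + (S(3) − 0.75)(1 − w)] / [1 − S(3)w], where w is the probability of still breastfeeding at 3 months.
  - Median weaning 4 months, w = 0.595: 0.143/0.447 = 32%.
  - Median 6 months, w = 0.707: 0.122/0.342 = 36%.
  - Median 9 months, w = 0.794: 0.107/0.261 = 41%.

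*Duration = weaning time only:* by independence every stratum has 1 − 0.75 = 25%.

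**Within-subgroup tests and the between-subgroup question.** The base sample size of 292 in Section 10 (10% v 25%, 90% power, two-sided 0.05) reproduces with a continuity correction, 2 × 146. Two equal halves give 73 per arm per subgroup; from 390 women, 97. Power within one half is 0.668 or 0.79. With the same true effect in both halves, the chance that one is significant and the other not is 2p(1 − p): 2 × 0.668 × 0.332 = 44%, or 2 × 0.79 × 0.21 = 33%.

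Approximate power for an interaction (15 points in one half, none in the other): variance = (0.1875 + 0.09 + 2 × 0.1875)/n = 0.6525/n. For n = 97, Φ(0.15/0.0820 − 1.96) = 45%; for n = 73, Φ(0.15/0.0945 − 1.96) = 35%.

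**The case against.** The best defence is that most listed subgroups are baseline by nature, that the psychosocial scales are also taken antenatally, and that the and/or wording allows the analyst to use only those readings. The first two points stand and narrow the concern to one group of factors. The third does not remove it: the objective itself names postnatal measurement, and the analysis text repeats it.

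A reader might infer that the plan will produce spurious subgroup effects. The documents do not support that. Bias from a postnatal measure needs the arm to change the measure; with no shift it was zero.

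A reader might also set the 13% and 7% against 25% in Arm A and take the ratios as the protocol's expected error. Section 10 states neither that definition of duration nor that contrast, and the clause can be read as description within Arm B. The model also makes default irreversible, whereas the endpoint combines a visit at 9 to 12 months with viral suppression, and the protocol refers defaulters back to care. Nor is the clause part of objective 2.3; it belongs to the primary objective.

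The absence of a named interaction test is weak ground by itself, since an analysis plan not shown may supply it. Multiplicity is not pressed: the list gives about 13 factors, and the protocol openly declares no adjustment and secondary status. Finally, replacing duration by area of residence is tempting, but the protocol shows address only as locator information, not as an analysis variable.

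**Conclusion.** The point holds in limited form. The protocol itself permits subgroups on psychosocial characteristics measured after allocation, so those within-subgroup comparisons can be biased under the null if the care setting affects the measure. Under the stated simulation assumptions the bias is about 2 to 8 percentage points; with no shift it is nil. Demographic, clinical-history and antenatal-ART subgroups are sound, and the primary intention-to-treat analysis is untouched.

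The duration stratification is a post-randomisation variable without an Arm A counterpart. Whether it misleads depends on a definition that the protocol does not give. Read as observed follow-up, it yields an apparent benefit of longer stay under the null (13% failure at 6 months or more against 25% overall, given constant-hazard default and independent weaning). Read as weaning time only, under the same independence, it yields no gradient.

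This should be corrected before analysis, but it does not threaten the trial's main conclusion.

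**What to change.** - **Objective 2.3 (Section 2 and Section 10):** restrict effect-modification subgroups to variables recorded up to and including visit 4, before randomisation. For the psychosocial scales, name the antenatal reading to be used (visit 2 or 3, as scheduled).
- **Same paragraph:** because the objective asks about variation between subgroups, report each arm-by-subgroup interaction with its confidence interval, labelled exploratory, alongside the subgroup estimates.
- **Duration clause (Section 10, primary objective):** define duration and make the analysis descriptive within Arm B, with no contrast against Arm A.
- **Postnatal measures:** use them only in analyses explicitly labelled non-randomised, descriptive or mediation.

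The cost is wording; the psychosocial scales are already collected before randomisation. The price is low power for interactions (about 35% to 45% in the example above) and no effect-modification claims from postnatal measures.
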